## Abstract

**Background:**

Hepatic resection is still associated with significant morbidity. Although the period of parenchymal transection presents a crucial step during the operation, uncertainty persists regarding the optimal technique of transection. It was the aim of the present randomized controlled trial to evaluate the efficacy and safety of hepatic resection using the technique of stapler hepatectomy compared to the simple clamp-crushing technique.

**Methods/Design:**

The CRUNSH Trial is a prospective randomized controlled single-center trial with a two-group parallel design. Patients scheduled for elective hepatic resection without extrahepatic resection at the Department of General-, Visceral- and Transplantation Surgery, University of Heidelberg are enrolled into the trial and randomized intraoperatively to hepatic resection by the clamp-crushing technique and stapler hepatectomy, respectively. The primary endpoint is total intraoperative blood loss. A set of general and surgical variables are documented as secondary endpoints. Patients and outcome-assessors are blinded for the treatment intervention.

**Discussion:**

The CRUNSH Trial is the first randomized controlled trial to evaluate efficacy and safety of stapler hepatectomy compared to the clamp-crushing technique for parenchymal transection during elective hepatic resection.

**Trial Registration:**

ClinicalTrials.gov: NCT01049607

## Background

Hepatic resection forms the cornerstone of therapy for a variety of benign and malignant diseases of the liver [1]. While advances in patient selection, surgical technique, perioperative management and imaging tools reduced mortality substantially, morbidity of patients undergoing hepatic resection remains as high as 30-60% even at high-volume centers [2-7]. Due to the risk of intraoperative hemorrhage as well as postoperative morbidity (e.g. bile leakage, posthepatectomy hemorrhage), the period of actual transection of the liver parenchyma represents a crucial step during hepatic resection. Various studies could indeed demonstrate intraoperative hemorrhage as predictor of poor perioperative outcome in patients undergoing hepatic resection [1,8]. Although various devices have been developed to facilitate parenchymal transection with the ultimate aim to reduce intraoperative blood loss [9], a recent systematic review and meta-analysis failed to show a benefit of these tools compared to the simple clamp-crushing technique [10]. However, to the present there is no randomized controlled trial (RCT) evaluating the technique of stapler hepatectomy. Based on the well-established role of stapling devices in various surgical fields and their common use for division of hepatic veins and portal branches [11-13], vascular staplers may facilitate rapid division of the liver parenchyma with immediate sealing of vascular and biliary structures. In theory, these features enable hepatic resection to be being carried out with less intraoperative blood loss as well as lower operation time.

### Existing evidence and need for the trial

Several recent systematic review articles including a Cochrane review on transection techniques showed that there is a lack of high-level evidence, i.e. randomized controlled trials, on the use of stapling devices for parenchymal transection in elective hepatic resection [9,10,14,15]. While there are several articles on the technique of stapler hepatectomy as well as retrospective non-controlled studies [16-18], there is currently no RCT evaluating efficacy and safety of stapler hepatectomy compared to standard technique of parenchymal transection. The largest single-center experience on stapler hepatectomy has been reported from the Department of Surgery, University of Heidelberg. This analysis comprised 300 patients who underwent hepatic resection using the technique of stapler hepatectomy for transection of the parenchyma [19]. Even though this report and others suggests stapler hepatectomy to be rapidly feasible as well as effective and safe in controlling intraoperative blood loss [14,20], it's retrospective, non-randomized study design does not justify general recommendations.

### Aim of this trial

There is clinical uncertainty and ongoing discussion among liver surgeons regarding the optimal method of parenchymal transection in patients undergoing elective hepatic resection. While the clamp-crushing technique still represents the reference technique for routine liver resections [10], transection of liver parenchyma using vascular staplers may offer a new and safe technique potentially reducing intraoperative blood loss, operation time as well as peri-operative morbidity. As morbidity of patients undergoing hepatic resection remains high, approaches to reduce peri-operative complications are urgently required. Due to the lack of evidence it has to be evaluated, if the technique of stapler hepatectomy decreases intraoperative blood loss as a known predictor of peri-operative morbidity compared to the clamp-crushing technique. In case of comparable or more favorable secondary outcomes such as peri-operative mortality, transection time and need for re-interventions, this advantages would favor stapler hepatectomy as a routine technique for elective liver resections. As RCTs are generally considered to generate the most valid scientific evidence on a treatment's effects, the efficacy and safety of stapler hepatectomy needs to be evaluated in a randomized fashion.

## Methods/Design

### Trial population and patient recruitment

Patients scheduled for elective hepatic resection at the Department of General-, Visceral- and Transplantation Surgery, University of Heidelberg will be screened for enrollment into the trial. Patients meeting the eligibility criteria will be enrolled into the study. Informed consent is obtained at least on the day before surgery.

#### Subject Inclusion Criteria

Subjects matching the following criteria are eligible for inclusion into the clinical trial:

• Patients scheduled for elective hepatic resection

• Stapler hepatectomy and clamp-crushing feasible based on preoperative imaging

• Age equal or greater than 18 years

• Informed consent

#### Subject Exclusion Criteria

Subjects matching any of the following criteria must not be included into the clinical trial:

• Concomitant extraheptic resection planned

• Participation in concurrent intervention trials

• Expected lack of compliance

• Impaired mental state or language problems

### Study objectives and endpoints

The primary objective of this trial is to show that intraoperative blood loss during elective hepatic resection can be reduced by stapler hepatectomy as compared to the clamp-crushing technique.

The primary efficacy endpoint of the CRUNSH Trial is total intraoperative blood loss [ml], which is defined as blood loss from skin incision until closure of the skin. Intraoperative blood loss is measured according to the blood collected in the suction containers. Spilling water and ascites is subtracted. Furthermore, swabs are squeezed and their content will also be sucked and added to the fluid collected in the suction containers. To obtain a more precise estimate for the individual patient patient's individual transection area will be considered as a continuous covariate multivariate analysis. The transection area will be assessed using an imprint of the resected specimen on a paper sheet with a known density of 80 mg/m^2^.

To further evaluate efficacy and safety of stapler hepatectomy compared to the clamp-crushing technique, a set of general as well as surgical variables are documented as secondary endpoints [21]. The secondary endpoints of the trial are summarized together with their definition in Table 1.

**Table 1 T1:** Secondary endpoints of the CRUNSH Trial

Secondary endpoint	Definition and assessment of outcomes
*Blood loss during liver transection [mL]*	Blood loss from beginning of parenchymal transection until minor oozing is stopped. To assess blood loss during liver transection the suction device will be connected to a new suction container for the period of actual hepatic transection.
Blood transfusion:	Administration of blood transfusions is documented for the intraoperative and postoperative period until 48 hours postoperatively. Documentation includes number of patients who received blood transfusions as well as amount of transfused packed red blood cells (PRBC) [units].
Operation time [min]:	Time from skin incision to placement of last skin staple/suture.
Liver transection time [min]:	Time from beginning to end of liver transection.
Duration of postoperative hospital stay [days]:	Time from day of operation to day of discharge.
Duration of ICU stay [days]:	Time on the Intensive Care Unit (ICU). Patients' stay in the recovery room and Intermediate Care (IMC) unit exceeding 24 hours is considered as ICU stay.
Morbidity:	The following predefined complications are documented within the CRUNSH Trial: Posthepatectomy hemorrhage [23]: Drop of hemoglobin level > 3 g/dl after the end of surgery compared to postoperative baseline level and/or any postoperative transfusion of PRBCs for a falling hemoglobin and/or the need for invasive re-intervention (e.g. embolization or re-laparotomy). Postoperative biliary leakage [24]: Presence of bile fluid (bilirubin level more than three times the serum level) in the abdominal cavity or drains on or after postoperative day or the need for reintervention (i.e. interventional drainage and/or relaparotomy due to bile fluid collections or biliary peritonitis). Further biliary complications: Biliary complications such as postoperative biliary stricture detected via ERCP and/or MRCP Intraabdominal fluid collection/abscess: Intraabdominal fluid collection detected on any imaging modality (e.g. ultrasound, CT scan) associated with abdominal discomfort/pain and/or elevation of infectious parameters. Posthepatectomy liver failure [25]: Increased INR or need of coagulation products (FFP, coagulation factors) to normalize the INR and increased serum bilirubin on or after postoperative day five. Pneumonia: Pulmonary infection with evidence of increased infection parameters (CRP > 2 mg/dl and/or leukocytes > 10 0000/ml) which are unlikely to be caused by a different pathologic process and evidence of pulmonary infiltrates on chest x-ray, requiring antibiotic therapy.
In-hospital mortality:	Death due to any reason within the patient's initial hospital stay.
Liver biochemical tests:	Serum levels of Alanine-Aminotransferase (ALT), Aspartate-Aminotransferase (AST), Gamma-glutamyl transferase (GGT), Quick's time/INR, Total Bilirubin, Albumin on postoperative day 1, 3 and 5.
Need for portal triad clamping:	Need for clamping of the hepatic pedicle to control intraoperative hemorrhage.
Resection margins	The proportion of patients with malignant tumors who have a positive resection margin will be documented.
Need for invasive re-interventions:	Invasive re-interventions such as placement of interventional drains, ERCP with stent placement and re-laparotomy within 30 days after the index operation or during patients' initial hospital stay.

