### Statistical analysis

Statistical methods are used to assess the quality of data, homogeneity of treatment groups, endpoints and safety of the two intervention groups. The confirmatory analysis is performed on the basis of an intention-to-treat (ITT) population and with respect to ITT principles.

Categorical data are summarized by means of absolute and relative frequencies (count and percent). Continuous data are presented by means of the following summary statistics: the number of observations, median, minimum, median and maximum. Wherever appropriate, data are visualized by box-whisker plots or histograms. The primary efficacy endpoint is amount of total intraoperative blood loss. The underlying two-sided null-hypothesis is that both study interventions lead to similar intraoperative blood loss:

$${\text{H}}_{0}:\mu 1-\mu 2=0$$

The alternative is that one intervention performs better than the other:

$${\text{H}}_{1}:\mu 1-\mu 2\neq 0$$

A confirmatory intention-to-treat analysis (2-sided test), including all patients as randomized, is performed on the amount of intraoperative blood loss between the two groups. Analysis of covariance (ANCOVA) is used to detect possible treatment differences with intraoperative blood loss as dependent variable, area of resection and CVP during transection as continuous covariates and type of intervention as factor. The sample size calculation is based on a two-sided t-test, and it can be assumed that evaluation with analysis of covariance has the same or even higher power.

Secondary endpoints will be analyzed in an exploratory way, using appropriate statistical methods based on the underlying distribution of the data. All analysis will employ SASα Version 9.1.

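### The leukocyte threshold in the pneumonia definition (Table 1) is misprinted in digits and unit, so as written that limb does not discriminate; minor, correct before pneumonia is compared by group

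*Protocol article*

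**What the plan says.** In the protocol article, section Study objectives and endpoints, Table 1 (row Morbidity), pneumonia is one of several predefined complications. The definition opens with "Pulmonary infection with evidence of increased infection parameters" and puts numbers on this in parentheses: "CRP > 2 mg/dl and/or leukocytes > 10 0000/ml". The raised parameters must be unlikely to have another cause, and the patient must also have "evidence of pulmonary infiltrates on chest x-ray, requiring antibiotic therapy".

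The leukocyte threshold appears nowhere else in the article, so no second statement of it is available to correct the first. Under Blinding, postoperative outcomes are assessed by a third party who does not know the allocation. Under Statistical analysis, the article states: "Secondary endpoints will be analyzed in an exploratory way".

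**The concern.** The string "leukocytes > 10 0000/ml" is not a properly grouped number, and with the stated unit it describes a count far below what blood normally contains. A threshold that everyone exceeds cannot identify an increased value. Since either limb alone is enough, a leukocyte limb that is always true also removes the CRP limb from the decision.

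This is a decision threshold in a predefined outcome. An assessor working from the printed text must either apply a numeric test that excludes nobody or replace it with a personal reading. What is at stake is the specificity of the pneumonia count. A looser definition applied equally to both groups would tend to pull a relative difference towards none. The section Aim of this trial says that comparable secondary outcomes would count in favour of the stapler, although pneumonia is not among the examples it names.

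**Working it through.** **Inputs from Table 1.** The leukocyte threshold as printed; the CRP threshold of 2 mg/dl; the *and/or* link between them; the remaining clauses of the definition.

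**Assumption.** The article gives no normal range. I take a usual adult count as about 4,000 to 10,000 per microlitre, and 500 to 1,000 per microlitre as marked leukopenia.

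**Step 1: convert the printed figure** (1 ml = 1,000 microlitres).
- Read as 100,000 per ml: 100,000 / 1,000 = 100 per microlitre.
- Read as 10,000 per ml (one zero surplus): 10,000 / 1,000 = 10 per microlitre.

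**Step 2: compare with plausible counts.**
- Usual range: 4,000 to 10,000 per microlitre × 1,000 = 4 to 10 million per ml. This is 40 to 100 times the 100,000 per ml reading and 400 to 1,000 times the 10,000 per ml reading.
- Marked leukopenia: 500 to 1,000 per microlitre = 500,000 to 1,000,000 per ml, still 5 to 10 times the higher reading.

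Only a count at or below 100 per microlitre would fail the 100,000 per ml reading, so the result does not depend on the exact range assumed.

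**Step 3: try the other repairs.**

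| Reading | Per microlitre | Leukocyte limb |
|---|---|---|
| 100,000 per ml (literal) | 100 | met by essentially everyone |
| 10,000 per ml (digits changed only) | 10 | met by essentially everyone |
| 100,000 per microlitre (unit changed only) | 100,000 | met by almost no one |
| 10,000 per microlitre (both changed) | 10,000 | separates usual from raised counts |

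Changing the digits alone or the unit alone does not give a working threshold. The last row is arithmetic on the printed digits; the article does not confirm it as the intended value.

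**Step 4: follow the logic.** The numeric test is (CRP above 2 mg/dl) OR (leukocytes above the threshold). If the second limb is always true, the test is always true. A patient with CRP above 2 mg/dl passes under every reading. Classification can therefore change only in a patient who meets the other clauses, has CRP at or below 2 mg/dl, and has a count that is not truly raised.

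**Step 5: bound the size.** Let p be the share of candidates (patients meeting the other clauses) with CRP above 2 mg/dl. The share that the misprint can affect is at most 1 − p. The article gives no p. If, purely as an assumption, p lies between 80% and 100% in the days after major open liver surgery, the bound is 1 − 0.80 = 20% down to 1 − 1.00 = 0% of candidates. The true share is lower still where candidates with low CRP have a raised count.

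**The case against.** The strongest reply is that this is an obvious misprint. The definition requires in words that the parameters be increased, and a count exceeded by everyone contradicts that wording. A sensible assessor would not apply it literally, and only one of the four readings works, so assessors correcting it would probably arrive at the same value. The article condenses a longer protocol, and the CRF is not shown; both may carry the right figure. A micro sign lost in converting the PDF to text is also possible.

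Much of this stands. It is very probably typographical, and nothing shows that assessors used the printed figure or corrected it in different ways. But a lost micro sign would explain only the unit, not the surplus zero, and restoring it alone gives 100,000 per microlitre, which also fails. Nor is this a detail left to a fuller document: the article states the threshold and states it wrongly.

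A reader might go further and infer three things that the article does not support:
- **That the pneumonia definition is void, or that any treated infiltrate would count.** Only the numeric test is lost. The requirement of a pulmonary infection, the exclusion of other likely causes, the infiltrate and the antibiotic therapy all remain.
- **That the comparison between arms is biased.** One definition applies to both groups, and the assessor is blinded. No mechanism is shown by which the error would act differently by arm.
- **That the main result is affected.** The primary endpoint is intraoperative blood loss. Neither the sample size nor the primary analysis of covariance uses this definition.

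**Conclusion.** The threshold is wrong as printed, in both digits and unit. Taken literally, the leukocyte limb is met by essentially every patient and, through *and/or*, the numeric infection-parameter test is always met. This rests on one assumption from outside the article, that blood leukocyte counts run in the thousands per microlitre, and it would survive any plausible change to that range.

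The consequence is limited. Only patients who satisfy the rest of the definition with CRP at or below 2 mg/dl and a normal count could be misclassified. Their number cannot be derived from the article and is probably small. The error touches one component of a secondary endpoint that is analysed in an exploratory way. Severity: minor.

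**What to change.** 1. Check the digits and unit of the leukocyte threshold in Table 1 against the full protocol and the CRF.
2. Have the investigators confirm the threshold they intended. The digits suggest 10,000 per microlitre, but the article does not settle it.
3. Correct Table 1, and the CRF if it carries the same figure.
4. Before pneumonia is compared by group, confirm that assessors used one threshold throughout, and record which.

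The cost is one corrected figure and a short check of how pneumonia was assessed. The design, the sample size and the primary analysis do not change.

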### Trial implementation

Patients scheduled for elective hepatic resection are screened consecutively for inclusion into the trial. All patients screened for the CRUNSH Trial are documented in the screening log. Patients meeting the inclusion criteria are enrolled in the trial. Informed consent has to be obtained at least on the day prior to surgery. Study visits within the CRUNSH Trial are displayed in Table 3.

**Table 3 T3:** Flow chart of the CRUNSH Trial

	Screening	Intervention	Follow Up		
	**Visit 1** **(up to 5 days before surgery)**	**Visit 2** **(day of surgery)**	**Visit 3** **(POD 1)**	**Visit 4** **(POD 3)**	**Visit 5** **(POD 7 or day of discharge)**

**Eligibility criteria Informed consent**	·				
**Medical history**	·				
**Demographics**	·				
**Physical examination**	·				
**Laboratory tests**	·		·	·	·
**Randomization**		·			
**Trial intervention**		·			
**Intraoperative parameters**		·			
**Postoperative parameters**			·	·	·

POD, Postoperative day

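### Invasive re-interventions are counted to 30 days, but the visit schedule ends at day 7 or discharge and no later ascertainment is stated

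*Protocol article*

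**What the plan says.** Four places in the protocol article bear on this.

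- **Endpoint definition (Study objectives and endpoints, Table 1).** Need for invasive re-interventions covers interventional drains, ERCP with stent and "re-laparotomy within 30 days after the index operation", with the initial stay as an alternative window.
- **Visit schedule (Trial implementation, Table 3).** The text says that "Study visits within the CRUNSH Trial are displayed in Table 3". The last column is Visit 5, at "POD 7 or day of discharge". There is no later visit, telephone contact or readmission check, and the table does not say which of the two dates applies when they differ.
- **Use of the endpoint (Aim of this trial).** Need for re-interventions is one of the named secondary outcomes that would support stapler hepatectomy as the routine technique, provided they are no worse than with clamp-crushing.
- **Status and assessment (Statistical analysis; Blinding).** Secondary endpoints are exploratory. Postoperative outcomes are assessed by a third party who does not know the allocation.

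**The concern.** The endpoint promises a 30-day observation period that the schedule does not provide. A drain placed for a late collection, or a stent for a late bile leak, after the patient has gone home falls inside the definition but after the last scheduled assessment.

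Two things are at stake. First, the rate may be too low in both arms, and two under-counted rates can look reassuringly similar. Second, if events are captured only up to discharge, observation time equals length of stay. Length of stay is a secondary endpoint that the transection technique could change, so the arm that goes home sooner would have less time in which a re-intervention could be recorded.

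**Working it through.** The plan gives no figure for this endpoint to reproduce, so the check sets the two tables side by side and measures the gap.

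**Step 1: does the gap depend on how Visit 5 is read?** Inputs: the 30-day window (Table 1) and Visit 5 (Table 3).

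- If Visit 5 is the earlier of day 7 and discharge, the last contact is never after day 7, so at least 30 − 7 = 23 days follow it.
- If it is the later of the two, the last contact is on day 7 or at discharge, so the uncovered part is at most 23 days. It reaches zero only for a stay of 30 days or more.

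The gap exists under both readings; only its length changes.

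**Step 2: how long is the gap?** Uncovered days = 30 − L, with L the day of last contact. The article gives no length of stay, so the values of L other than 7 are assumptions.

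- L = 5: 25 days, 25/30 = 83%
- L = 7: 23 days, 23/30 = 77%
- L = 10: 20 days, 20/30 = 67%
- L = 14: 16 days, 16/30 = 53%
- L = 21: 9 days, 9/30 = 30%

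**Step 3: what could this do to the rate?** This is an illustration; none of its rates is in the article. Let r be the true 30-day rate, let H = −ln(1 − r), and suppose that nothing is captured after day L (a worst case). The observed rate is 1 − exp(−H·(L/30)^k), with k = 1 for a constant hazard and k = 0.5 for events concentrated early.

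For r = 10%, H = 0.1054:

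- L = 7: 1 − exp(−0.1054 × 0.2333) = 2.4% (k = 1); 1 − exp(−0.1054 × 0.4830) = 5.0% (k = 0.5)
- L = 14: 1 − exp(−0.1054 × 0.4667) = 4.8% (k = 1); 1 − exp(−0.1054 × 0.6831) = 6.9% (k = 0.5)

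At L = 7, the same formula over both shapes gives 1.2% to 2.5% for r = 5% and 3.7% to 7.6% for r = 15%.

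**Step 4: how large is that against chance?** With 65 patients per arm and r = 10%, 6.5 events per arm are expected. At L = 7 about 65 × 0.0243 = 1.6 to 65 × 0.0496 = 3.2 would be recorded. If one arm were observed to day 7 and the other to day 14, the spurious difference would be 4.80 − 2.43 = 2.4 points (k = 1) or 6.94 − 4.96 = 2.0 points (k = 0.5). The standard error of such a difference is √[(0.0243 × 0.9757 + 0.0480 × 0.9520)/65] = 3.3 points, or √[(0.0496 × 0.9504 + 0.0694 × 0.9306)/65] = 4.1 points. So the loss of events in both arms is the larger problem. Even with a full week's difference in stay, the distortion between arms is smaller than one standard error.

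**Step 5: is the window itself fixed?** No. Because the definition adds the initial stay, the window is the longer of 30 days and the stay, so it also varies with stay beyond day 30.

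**The case against.** The strongest reply is that no scheduled visit does not mean no data. This is a single-center trial, and Data management and quality assurance ties case report form entries to any examination or treatment and to source data, so recording is not confined to the Table 3 visits. The full protocol, which is not shown, may describe a record search. This stands in part: it rules out saying that late events are lost, and it makes in-hospital capture likely. It does not give a stated route for events after discharge. Nor is this only detail left out of a condensed article, because the article prints both a full endpoint definition and a visit schedule, and the two do not match. The laboratory days show the same lack of alignment: Table 1 ends with "Albumin on postoperative day 1, 3 and 5", while Table 3 has days 1, 3 and then 7 or discharge.

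A second reply is that secondary endpoints are exploratory. That is true and limits the weight of the point. It does not remove the problem from an outcome that Aim of this trial uses for its recommendation.

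A reader might go further and infer that mortality and hospital stay are also compromised. The documents do not support that. Mortality is "Death due to any reason within the patient's initial hospital stay" and stay is "Time from day of operation to day of discharge". Both end at discharge by definition and can be read from the hospital record without a study visit.

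A reader might also infer that one arm's events would be captured and the other's not. Nothing in the article suggests capture that differs by arm, and the blinded assessor argues against it. Any imbalance would have to come through different lengths of stay.

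**Conclusion.** The point holds in a limited form. Tables 1 and 3 conflict: re-interventions are defined to day 30, and no means of collecting them between discharge and day 30 is stated. Post-discharge re-interventions may be missed, and the observed rate then depends on length of stay. For a last contact on day 7, 77% of the window follows the last scheduled assessment.

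The conclusion about the tables rests on the article alone and holds under either reading of Visit 5. The size of any under-count rests on assumed event rates, timing and stay, and on no capture after the last contact, so the rates worked out above are bounds for illustration and not estimates. One exploratory secondary endpoint is affected; the intraoperative primary endpoint and its sample size are not. The change is worth making because it is cheap and the endpoint feeds the trial's recommendation, but it does not threaten the main result.

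**What to change.** 1. Add to Table 3 one day-30 telephone or record check for all patients, made by the blinded assessor and covering re-intervention and readmission.
2. In Table 1, count re-interventions over a fixed 30 days after the operation in both arms, in place of the window that lengthens with the stay.
3. State whether Visit 5 is the earlier or the later of day 7 and discharge. Keep a scheduled laboratory assessment there: Visit 5 is the only one after day 3 in Table 3, and the liver failure definition uses values from day 5 onward. Reconcile the laboratory days in the two tables at the same time.
4. State that complications are recorded to discharge. Table 1 says that "The following predefined complications are documented within the CRUNSH Trial" but gives no closing day.

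The cost is one brief contact or record check per patient, about 130 in all (65 per group), plus corrections to two tables. The primary analysis does not change.

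Redefining the endpoint as the initial stay only would cost less and would remove the conflict between the tables, but it is not advised: it would make the window equal to length of stay and so fix in place the dependence that needs removing.
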